# Efficacy of diode-emitting diode (LED) photobiomodulation in pain management, facial edema, trismus, and quality of life after extraction of retained lower third molars

**DOI:** 10.1097/MD.0000000000012264

**Published:** 2018-09-14

**Keywords:** edema, LED, pain, photobiomodulation, randomized clinical trial, tooth extraction

## Abstract

**Background::**

In dentistry, one of the most common surgical procedures is the removal of retained third molars. This surgery generates great morbidity to the participants for causing pain, edema, and trismus due to surgical trauma. The objective of the present study is to evaluate the efficacy of photobiomodulation with light emitting diode (LED) in the control of pain, facial edema, trismus, and quality of life resulting from the extraction of retained lower third molars.

**Methods::**

A randomized, double-blind, placebo-controlled clinical trial involving 38 adult participants, who meet the criteria of eligibility and agree to participate in the study. Before the surgeries are performed, the facial and mouth opening measures of all the participants will be taken. Immediately after the surgeries, participants will be randomized into 2 groups. In the LED group, participants will receive LED applications (intra oral with 660 nm, 12J and extraoral with 850 nm, 108J) in the immediate postoperative, first and second days after the surgical procedure. In the control group, the participants will be attended in the same way as in the LED group, however, the person in charge of the application will simulate the irradiation. Pain (EVA and NRS-101), postoperative edema, trismus, temperature, dysphagia, and hematoma will be evaluated after 1, 2, 5, and 7 days. The oral health impact profile (OHIP-14 Questionnaire) and anxiety analysis (Beck anxiety inventory -BAI) questionnaires will be applied preoperatively and 7 days after treatment. The appropriate statistical tests will be applied for each specific analysis in a significance level of 5%.

**Discussion::**

Although the use of low-power laser in the postoperative has shown good results in the control of postoperative sequelae, this is the first study on the efficacy of the use of LED in this situation.

## Introduction

1

Photobiomodulation (PBM) is an emerging technique using red or near infrared light (low-power laser or light emitting diode [LED]) to modulate inflammation, accelerate wound healing, and reduce pain and discomfort in different clinical situations.^[1,2]^ The efficacy of PBM depends on the parameters, such as wavelength, power output, and energy. Different clinical situations require different PBM protocols. Most of the research on PBM in dentistry was carried out with low power/intensity lasers and some protocols are already well established using these lasers.^[2]^ However, few studies in dentistry were developed using LEDs, and most of them were performed to prevent/treat oral mucositis.^[3]^

Some studies have demonstrated a beneficial effect of LED (670 nm) on the incidence and severity of oral mucositis in participants undergoing oncological treatment.^[4–6]^ However, the near-infrared light in the 850 nm range has been shown to be capable of promoting vasodilation and the production of growth factors, as well as angiogenesis, leading to wound healing.^[7,8]^

In dentistry, one of the most common surgical procedures is the removal of retained third molars.^[2,9]^ This surgery generates great morbidity to the participants by causing pain, edema, and trismus due to surgical trauma.^[2,10,11]^ In recent years, several studies have shown beneficial effects of low intensity laser therapy in the postoperative period of lower third molar extractions.^[12–14]^. Despite the beneficial effects of LEDs on pain control and repair described in the literature, no studies were found to evaluate the effect of the use of LEDs in the postoperative period of third molar surgery. This is a relatively new technology and it is still under investigation especially in clinical trials.

The objective of the present study is to evaluate the efficacy of LED photobiomodulation in pain control, facial edema, trismus, temperature, dysphagia, hematomas, and quality of life after the extraction of retained lower third molars.

## Methods/design

2

### Type of study

2.1

A randomized, double-blind, placebo-controlled clinical trial will be conducted to determine the efficacy of diode-emitting diode (LED) PBM on the adverse effects of extraction of retained lower third molars. The study will be conducted at the Faculty of Dentistry of UFRGS, Department of Surgery and Orthopedics (DCO), from May 2018 to May 2019.

The study will be conducted in accordance with the guidelines of good clinical practice and has been approved by the Research Ethics Committee of UFRGS under process number 82570818.0.0000.5347. It follows the 466/2012 resolution of the National Health Council. After clarification and authorization of participants (or their guardians, for those under age) they shall sign a Free and Informed Consent Form.

The protocol is in accordance with the 2013 SPIRIT (Standard Protocol Items: Recommendations for Interventional Trials) Statement. The SPIRIT checklist can be found as an additional file and Figure 1 is the SPIRIT figure. SPIRIT was developed to provide guidance in the form of a checklist of recommended items to include in a clinical trial protocol, to help improve its content and quality.

**Figure 1 F1:**
[figure not shown]
SPIRIT figure as recommended by 2013 SPIRIT Statement.

### Trial registration

2.2

Clinicaltrials.gov as NCT03442166, first posted February 22, 2018 and last updated May 17, 2018; https://clinicaltrials.gov/ct2/show/NCT03442166

### Sample calculation

2.3

A sample calculation based on the parameters of variability of the article of Eshghpour, Ahrari ^[13]^ based on the pain analysis of the participants on the 3rd postoperative day evaluated by a visual analog scale (VAS) was performed. Using a power of 80% and level of significance of 5%, a minimum sample size of 17 cases per group was obtained, making a total of 34 participants for the study. Winpepi software version 10.5 was used for this calculation. Considering a loss of 10%, based on the study that was used for the sample calculation, a loss of 2 participants per group should be predicted. Therefore, the total number of participants to be selected will be 38 individuals.

*Inclusion criteria*:Need of surgical removal of retained lower third molars;Agree to participate in the study after reading and signing the Informed Consent Term;Participants with indication for extraction of lower third molars (recurrent infections, bad position, and orthodontic indication) or professional written indication, healthy patients (negative medical history), systolic blood pressure lower than 140 mm Hg, and diastolic blood pressure lower than 90 mm Hg and heart rate values of 70 ± 20 beats/minute. The upper and lower central incisor teeth must be present.

*Exclusion criteria*:Systemic diseases, chronic pain or neurological and psychiatric disorders;Smokers;Using anti-inflammatories, analgesics or bisphosphonates in the last 15 days;Present active pericoronarite;Pregnant;Breastfeeding;Severe temporomandibular disorders;Photosensitivity history;Allergic to any drug used in the research (paracetamol, chlorhexidine 2%);Participants presenting radiolucent images associated with the teeth to be extracted;Participants who present any type of complication during surgery (hemorrhage, operative difficulty, time greater than 90 minutes of surgery), as these cases are not in the standard expected for third molar surgeries. In this case, the central action analgesic will be prescribed. These data will not be part of the statistical analysis but will be described and discussed.

### Recruitment and randomization

2.4

Thirty-eight participants of both genders referred to the Faculty of Dentistry of UFRGS who need to perform the removal of lower third molars will be selected. Participants will be approached by means of an oral invitation to be conducted after verifying the eligibility criteria of the subject for the research.

To randomly distribute the subjects in the 2 experimental groups, a draw will be made with numbers. As the numbers are drawn, they will compose the experimental groups. Opaque envelopes will be identified with each number and inside it a sheet containing the information of the corresponding experimental group will be inserted according to the order obtained in the draw. The envelopes will be sealed and will remain sealed in numerical order in a safe place until the time of the surgeries. The drawing and preparation of the envelopes will be performed by a person who is not involved in the study.

Participants will be evaluated by the surgeon and when they meet all eligibility criteria previously described, they will be included in the study. All will be submitted to the same surgical protocol. Immediately after the surgeries, the researcher responsible for applying the LED will remove and open one envelope (without changing the numerical sequence of the other envelopes) and perform the indicated procedure.

The 38 participants will be allocated in the experimental groups as follows:

LED group (n = 19): Participants will receive 3 applications of intraoral LEDs with 660 nm and extraoral with 850 nm (Oncollux, Cosmedical, São Paulo, SP, Brazil) in the immediate postoperative, first and second days after the surgical procedure. The intraoral irradiation will be performed with a 6 red LED cluster and in the extraoral site a 36 infrared LED cluster will be used. The parameters of red/infrared LED are describe in Table 1.

**Table 1 T1:**
[figure not shown]
LED parameters.

Control group (n = 19)—Participants will be attended in the same way as the LED group. The person in charge of the application will simulate the intraoral and extraoral irradiation by positioning the LED in the same locations described for the LED group, but the equipment will be kept off. So that the patient does not identify the sound of activation of the device (beep), it will be recorded, and connected at the time of application.

## Evaluations

3

### Preoperative assessment

3.1

#### Facial measures

3.1.1

Measurements of the distances between the corner of the eye and the angle of the mandible, between the tragus and the labial commissure, and between the tragus and the pogonium of each patient will be taken before the surgical procedure.

#### Mouth opening

3.1.2

The opening of the mouth will be measured by the distance between the incisal edges of the upper and lower central incisors using a 150 mm hand-operated caliper (ECCOFER, Curitiba, Paraná, Brazil) as previously described.^[15,16]^

### Surgery

3.2

The procedures will be performed by a surgeon specializing in maxillofacial surgery. The surgical material and the operative technique will be determined according to protocol for removal surgeries of retained third molars from School of Dentistry of UFRGS. The following procedures will be performed in each surgery: extra and intraoral antisepsis, infiltrative anesthesia by block and infiltrative terminal of the tooth and attached structures, isolation and drying of the operative field with gauze, incision with proximal extension of the teeth involved in order to allow access to the exposure surgical removal of the gingival flap, osteotomy for access (when necessary), muco-periosteal detachment, ostectomy, odontosection with electric motors (when necessary), aspiration of blood and liquids used for irrigation and washing of the operative field, detachment and removal of the gingival flap, avulsion of the dental element, irrigation and suture.

All participants will receive the following medications: Codeine 30 mg, paracetamol 500 mg to be used every 6 hours, in the first 24 hours. Then, they will use paracetamol 750 mg every 6 hours for the duration of the painful symptomatology. They will be asked for information on the amount of medicine ingested. The data of these participants will only be described, but not included in the analysis of the results. Such exclusion shall not prejudice the treatment.

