### Discontinuing intervention

5.3

The application of LEDs offers minimal risk, however, if during treatment, some participants report increased pain or display an infectious condition, measures such as the use of analgesics and/or antibiotics will be adopted according to clinical tolerance and individual assessment. These participants will be excluded from the study and will be followed up by the surgical team until resolution of the condition.

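### The analgesia paragraph keeps an undefined group out of the analysis: read literally it covers everyone, and read by analgesic intake it selects on pain after allocation

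*Protocol article*

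**What the plan says.** The second paragraph of section 3.2 (Surgery) has five sentences, in this order:

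1. "All participants will receive the following medications: Codeine 30 mg, paracetamol 500 mg to be used every 6 hours, in the first 24 hours".
2. "Then, they will use paracetamol 750 mg every 6 hours for the duration of the painful symptomatology".
3. "They will be asked for information on the amount of medicine ingested".
4. "The data of these participants will only be described, but not included in the analysis of the results".
5. "Such exclusion shall not prejudice the treatment".

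Two other sections also take participants out. Section 2.3 (Sample calculation), in the exclusion criteria, covers complications during surgery, for which a centrally acting analgesic is prescribed: "These data will not be part of the statistical analysis but will be described and discussed". Section 5.3 (Discontinuing intervention) provides that "if during treatment, some participants report increased pain or display an infectious condition, measures such as the use of analgesics and/or antibiotics will be adopted", and continues: "These participants will be excluded from the study and will be followed up by the surgical team until resolution of the condition". Section 5.1 (Ethics committee) adds that anyone who misses a scheduled session leaves the study.

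Sections 2.4 and 3.4 place the opening of the allocation envelope after surgery, once the suture is complete. Section 2.3 sizes the trial on VAS pain.

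**The concern.** Sentence 4 decides who enters every comparison, yet its subject is undefined. Nothing between sentences 1 and 4 names a subgroup, an intake threshold or an additional drug.

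The nearest topic is the amount of medicine taken. A natural attempt to make sense of the rule is therefore that participants who took more, or for longer, are described but not analysed. By the protocol's own sentence 2, intake after the first 24 hours follows pain. It arises after allocation, and LED is meant to change it. If LED works, such a rule removes more controls than LED participants, and removes the controls with the worst pain. That breaks the comparability created by randomisation, pulls the estimated difference towards zero and shrinks the sample.

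An undefined rule also leaves the choice of whom to drop open until intake data have been seen.

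**Working it through.** **Reproducing the plan's figure.** Section 2.3 gives 17 per group, 80% power, 5% significance and 10% loss. 17 / 0.9 = 18.9, rounded up to 19 per group, so 38 in total. This agrees with the plan. The 17 itself cannot be re-derived, because the article gives neither a difference nor an SD.

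**Implied effect (assumption: two-sided test).** Solving for the standardised difference that gives 80% power with 17 per group:
- normal approximation: (1.960 + 0.842) × √(2/17) = 0.96 SD;
- t-test: 0.99 SD, used below.

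With all 19 per arm analysed, 0.99 SD gives 84% power. With 17 per arm it gives the planned 80%.

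**Literal reading.** Analysed = 38 − 38 = 0.

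**Intake reading, removal unrelated to pain.** t-test at 0.99 SD, equal shares removed from both arms:
- 10% removed: 17 per arm, 80% power (the loss allowance is used up);
- 20% removed: 15 per arm, 75%;
- 30% removed: 13 per arm, 68%.

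**Intake reading, removal related to pain.** Assumptions:
- Pain is normal with SD 1, mean 0 in controls and −d in the LED arm, with d = 0.991.
- Intake is a standardised score with correlation r to pain within each arm, and its LED mean is lower by r × d.
- Everyone above a common cut-off c is removed, where c is set so that a share q of controls goes.

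With λ(a) = φ(a)/Φ(a), the analysed difference is d − r × [λ(c) − λ(c + r × d)].

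Worked case, r = 1 and q = 20%: c = 0.842, λ(0.842) = 0.350, λ(1.833) = 0.077, so the difference is 0.991 − (0.350 − 0.077) = 0.718.

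Power was simulated with 19 randomised per arm and a two-sided t-test:

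| r | Controls removed | LED removed | Analysed difference (SD) | Power |
|---|---|---|---|---|
| 1 | 20% | 3% | 0.72 | 65% |
| 1 | 30% | 7% | 0.63 | 54% |
| 0.7 | 20% | 6% | 0.84 | 71% |
| 0.7 | 30% | 11% | 0.79 | 64% |
| 0.5 | 20% | 9% | 0.91 | 74% |
| 0.5 | 30% | 15% | 0.88 | 67% |

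Repeated simulations move the powers by a point or two (53% to 55% for the lowest). Analysed controls average 19 × 0.8 = 15.2 or 19 × 0.7 = 13.3.

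**Complication reading.** The events in section 2.3 (haemorrhage, operative difficulty, surgery longer than 90 minutes) occur during surgery. The envelope is opened afterwards. Removal on those events alone does not depend on the allocated arm, so the table does not apply to it.

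**The case against.** A reader might infer that the analysis set must be either empty or selected on pain. The documents do not support that dichotomy. Section 2.3 uses the same pattern for surgical complications: an analgesic is mentioned, and the data are then described but not analysed. Sentences 4 and 5 could be that rule repeated out of place, in a section that is after all headed Surgery. On that reading nobody is removed for postoperative pain or intake. This possibility stands. However, section 3.2 mentions no complications, and section 2.3 already states the rule in full.

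It can also be said that sentence 4 concerns only the intake data, which would be reported descriptively. Sentence 5 weighs against this: it speaks of an exclusion that must not prejudice treatment, which fits people rather than a variable. Some ambiguity remains.

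The literal result of 0 analysed contradicts the powered comparison of 38 participants planned elsewhere in the article. It shows a wording error, not a real analysis set.

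The sizes are illustrative. The 0.99 SD effect, the exclusion shares and the intake model are not in the documents. The loss to 0.72–0.63 SD requires intake to track pain perfectly, so it is the extreme of the range. The starting 84% also assumes no other losses, whereas the plan's own figure is 80% at 17 per group.

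Finally, a condensed article may leave detailed outcome definitions to the full protocol or SAP. That is fair for the list of secondary outcomes. It does not excuse an exclusion rule that the article itself states and leaves without a subject.

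**Conclusion.** The point holds as a defect in a stated rule. As printed, the two sentences exclude a group that the paragraph defines only as all participants, and no reading leaves them usable without a change. If intake is the criterion, the exclusion comes after allocation and depends on pain. Under the assumptions above, the difference falls from 0.99 SD to between 0.91 and 0.63 SD, and power from 84% to between about 74% and 54%. Under a common cut-off with intake positively related to pain and a true LED benefit, the direction is towards zero; the amount depends on the share removed and on r.

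The documents do not establish that intake-based exclusion is intended, and the complication reading would avoid this bias. Section 5.3 does separately exclude participants for increased pain, so selection on pain is present in the article whatever section 3.2 means. Correcting section 3.2 alone would not remove it.

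**What to change.** - Delete sentences 4 and 5 from section 3.2. If the complication rule was meant, replace them with an explicit reference to section 2.3, restricted to events before the envelope is opened.
- State that no participant is removed from the analysis because of analgesic intake.
- Reconcile that statement with section 2.3 (complications), section 5.1 (missed session) and section 5.3 (increased pain or infection), saying for each whether data from randomised participants stay in the analysis. Without this step the new statement would sit beside rules that contradict it.
- Compare the amount of medicine ingested between arms as a supportive outcome, read alongside the pain scores. The amount is already recorded. The article does not mention recording a date of last use, so a duration-of-use outcome would need additional data collection and is not asked for here.

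The cost is a few sentences across four sections, with no new data and no change in sample size. The medication regimen and clinical follow-up are not part of this point.

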### Evaluation of the surgical procedure by the surgeon

3.3

At the end of the surgeries, the maxillofacial surgeon will record the following: the position of the retained tooth, the degree of difficulty of the procedure, the number of anesthesia tubes used, the occurrence of hemorrhage during surgery and during suturing and the duration of the surgery (from the first incision to the end of the suture).

The position of the included tooth will be determined based on the classifications proposed by Winter^[17]^ and by Pell and Gregory.^[18]^

The degree of difficulty of the surgery will be evaluated by the Prant scale modified by Amarillas-Escobar et al,^[19]^ which classifies the surgical procedure as follows: grade 1=extraction with only a forceps; grade 2=extraction with osteotomy; grade 3=extraction with osteotomy and coronal section; and grade 4=complex extraction.

### Procedures to guarantee double blinding in the postoperative period

3.4

After the suture is completed, the researcher responsible for applying the LED will open the envelope containing the information from the experimental group in which the patient will be inserted and proceed to the experiment. A single examiner will run the LED application and will not perform any type of evaluation. Surgical procedures will be performed by the same surgeon. The preoperative and postoperative evaluations (1, 2, 5, and 7 days postoperatively) will be done by an examiner who will not be aware of the group in which each patient is allocated. The information that will be obtained in the evaluations will be written in the evaluator's file. Participants will not be aware of whether or not they received LED irradiation because the person responsible for applying the LED will position the insert in the irradiation sites in all participants and will only trigger light when and where predicted in the specific experimental group. The characteristic sound of the device will be triggered by recording in the control group.

### Postoperative pain evaluation

3.5

In this project, we intend to apply 2 scales: the VAS and NRS-101. The VAS will be printed on the patient evaluation form and the subjects will be instructed by the evaluator to mark a point on the 10 cm line, indicating the intensity of their pain after 1.2, 5, and 7 days of the surgeries For the NRS-101 scale, the evaluators will ask participants to assign a number between 0 (no pain) and 100 (worst possible pain) that best represents the pain they are currently experiencing after 1, 2, 5, and 7 days of surgeries.

### Evaluation of postoperative edema

3.6

The evaluator will measure the distances between the corner of the eye and angle of the mandible, between tragus and labial commissure, and between tragus and pogonium^[14]^ of each patient 1, 2, 5, and 7 days after surgery.

